
##### Executive functions

Under the guidance of a trained member of the research team (1:1), in a quiet space outside the classroom (e.g., the library), individual children will be asked to work through three age-appropriate activities from the National Institute for Health (NIH) Toolbox (Gershon et al., 2010) to assess the three core executive functions. The NIH Toolbox is a comprehensive set of neuro-behavioral measurements that quickly assess cognitive, emotional, sensory, and motor functions from the convenience of an iPad. Each child will complete three cognitive activities lasting 15 min in total: inhibitory control is assessed through The Flanker Test (3 min), cognitive flexibility through the dimension card sort (4 min), and working memory via a list sorting task (7 min). The NIH toolbox has well-established validity and reliability for use with children aged 3–15 years (Weintraub et al., 2013).

##### Self-regulation

Children’s self-regulation will be assessed using the Strength and Difficulties Questionnaire (SDQ; Goodman, 1997; Stone et al., 2010), which will be completed by class teachers for each participating child at each time point. The SDQ is a brief behavioral screening questionnaire consisting of 25 items within five subscales (emotional, conduct, hyperactivity, peer and prosocial), and has demonstrated good reliability and validity across several studies (Essau et al., 2012). There are five items on each subscale with each item scored 0, 1, or 2. Scores therefore range from 0 to 10 for each subscale, with 10 indicating higher levels of difficulties (emotional, conduct, hyperactivity, peer subscales) or strengths (prosocial subscale) and 0 indicating lower levels. A total difficulties score is also generated by summing scores from all the scales except the prosocial scale, with scores ranging from 0 (low) to 50 (high).

Each child’s self-regulation will also be assessed by researchers using the RCS (Lakes, 2012, 2013). The RCS is an observer-rated measure of children’s responses to challenges in an obstacle course. The course is designed to vary demand and challenge and takes 10–15 min to complete in a school hall/outside school playground. The trained observer rates children on 16 items comprising bipolar adjectives (e.g., Vulnerable—Invincible), which are rated on seven-point scales (scored 1–7). Negatively worded items are reversed prior to aggregation, so that possible scores on all items ranged from 1 to 7, with higher scores indicating greater self-regulation. Items are summed to assess self-regulation within three subscales: “Cognitive” (six items, scoring range from 6 to 42), “Affective” (seven items, scoring range from 7 to 49) and “Physical/Motor” (three items, scoring range from 3 to 21).

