### Hypotheses

Based on previous literature (Morgan et al., 2013; Tompsett et al., 2017), we expect that children who participate in the *Linear* and *Non-linear* Pedagogy interventions will demonstrate greater improvements in movement competence compared to children following standard PE practice. It is also expected that children in the Non-linear Pedagogy intervention will demonstrate greater movement creativity but lower technical movement proficiency than children in the Linear Pedagogy group (Lee et al., 2014). Furthermore, children in Linear and Non-linear Pedagogy interventions will show greater gains across physical literacy elements (affective [perceived competence and motivation], cognitive [cool executive functions], cognitive-affective [self-regulation] and behavioral [physical activity]) than children in standard PE practice. Finally, it is also expected that the Non-linear Pedagogy intervention will see greater improvements in children’s affective (motivation), cognitive (cool executive functions: cognitive flexibility, working memory, and inhibitory control), cognitive-affective (self-regulation) domains than the Linear Pedagogy intervention (Lee et al., 2014; Alvarez-Bueno et al., 2017; Vazou et al., 2019).

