### Blinding and Randomization

For practical reasons, it will not be possible to blind the researchers, teachers, and coaches to group allocation. Following collection of headteacher consent, randomization will take place at the school (cluster) level. Schools will then be matched based on the number of students enrolled and level of deprivation identified using the school postcode (Ministry of Housing Communities Local Government, 2018). Following this, schools will be randomly allocated to an intervention condition or control group using a computer-based random number producing algorithm by an independent researcher not associated with the study. This method ensures that schools had an equal chance of allocation to each group.

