### Outcomes

Trained research assistants will undertake 2–3 days of data collection at participating schools across three time-points (see Figure 1). Demographic characteristics including child’s age, gender, ethnicity, and home postcode (used to classify children into deciles of deprivation level using the English indices of deprivation: Ministry of Housing Communities Local Government, 2018) will be collected at baseline through parent consent forms. A number of primary and secondary outcomes are measured through the study.

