#### Primary Outcome

##### Movement competence

Movement competence will be assessed through a battery of assessments to examine both technical movement proficiency and movement creativity across different domains (locomotor, object-control, and stability skills). All movement competence assessments will take place during school hours within the school hall or playground and video-recorded for later analysis. Trained research assistants who have established acceptable agreement (80%) in terms of intra-rater and inter-rater reliability with pre-coded videos, will complete analysis of video recordings.

Movement proficiency (technique) will be assessed using the Test of Gross Motor Development-3 (TGMD-3; Maeng et al., 2016) and the Test of Stability Skills (Rudd et al., 2015). Specifically, six locomotor (run, gallop, hop, skip, horizontal jump, slide) and seven object-control (two-hand strike, one-hand strike, one-hand dribble, two-hand catch, kick, overhand throw, underhand throw) skills will be assessed using the TGMD-3 (∼30 min to complete). Proficiency at stability skills will be assessed using the three tasks (log roll, rock, back support) from within the Test of Stability Skills (∼15 min to complete). The psychometric quality of these assessments has been well-established (Rudd et al., 2015; Maeng et al., 2016). Participants will receive a verbal explanation and single demonstration from the assessor and are then given one practice attempt before undertaking two trials of each skill.

Movement creativity will be assessed using the Divergent Movement Ability Assessment (Cleland, 1990), which requires children to complete three stations, a stability skill station, a locomotor skill station and object control skill station (∼15 min to complete). In the stability station, children are asked to make as many shapes on or around the bench as they can. In the locomotor station, children are challenged to find as many different ways to move around the obstacle course as possible. Finally, in the object-control skill station, children will be asked to play with a large ball in a designated area, showing all the different skills and ways that they can play with the ball. For every station, children will complete two 90 s trials, during which, every 30 s the child will get a predefined prompt from the research assistant to support and encourage the child.

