### Process Evaluation

Informed by the RE-AIM framework and previous literature (Glasgow et al., 1999; Linnan et al., 2002) as well as by the UK Medical Research Council guidance for process evaluation that advocates exploring context, implementation, impact and outcomes (Moore et al., 2015) a pragmatic process evaluation design will examine intervention *context*, *reach*, *dose*, *fidelity*, *acceptability implementation*, *impact*, *acceptability*, and *sustainability*.

*Reach* will be assessed using school administrative data on child demographics and school registers. Teachers (control schools) and SAMPLE-PE coaches (intervention schools) will be asked to log the number of PE lessons implemented at each school, and the duration of each PE lesson in minutes to determine. Direct observations of PE lessons by researchers and coaches’ logs will be used to examine *dose delivered*, *fidelity* and participant responsiveness (*dose received*). Specifically, in each intervention and a subsample of control schools, three lessons from each class (one in every 5-week phase of delivery) for a total of approximately 50 lessons will be audio- and video- recorded, using a wireless microphone and video camera (situated to capture the whole class and deliverer).

Video footage will subsequently be analyzed by trained researchers to assess whether the intervention was delivered as intended (*fidelity*) using developed observation checklists for Non-linear and Linear pedagogies, respectively. Intervention fidelity will be confirmed if (i) the Non-linear pedagogy intervention schools’ PE lessons show greater implementation of Non-linear pedagogical principles than Linear and control schools PE lessons, and (ii) the reverse is true for Linear pedagogy intervention schools’ PE lessons. Video recordings of PE lessons will also be retrospectively coded using established observation checklists to examine SAMPLE-PE coach (intervention schools) and teacher (control schools) behaviors in relation to promoting children’s moderate-to-vigorous physical activity (SOFIT+; Weaver et al., 2016; Fairclough et al., 2018) and supporting or thwarting children’s psychological needs for relatedness, competence, and autonomy (Smith et al., 2015). Researchers will also record the number of children participating in lessons, and the number of staff present and collect data on the themes and types of activities undertaken within the control group’s PE lessons.

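### The Response to Challenge Scale is a subjective rating scored by researchers whom the plan declares unblinded, so no self-regulation measure is protected against rater expectation

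*Protocol article*

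**What the plan says.** The Self-regulation section names two measures.

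- **Strengths and Difficulties Questionnaire (SDQ).** Class teachers complete it for each participating child at each time point.
- **Response to Challenge Scale (RCS).** "The RCS is an observer-rated measure of children’s responses to challenges in an obstacle course". "The trained observer rates children on 16 items comprising bipolar adjectives", each scored 1 to 7, and the raters are members of the research team: "self-regulation will also be assessed by researchers using the RCS".

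Under Blinding and Randomization the article gives practical reasons and states that "it will not be possible to blind the researchers, teachers, and coaches to group allocation". It makes no exception for people who only score outcomes.

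Three other sections bear on the point:

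- **Hypotheses:** "children in Linear and Non-linear Pedagogy interventions will show greater gains across physical literacy elements", with self-regulation listed among those elements. Non-linear Pedagogy is further expected to exceed Linear Pedagogy on self-regulation.
- **Outcomes:** "Trained research assistants will undertake 2–3 days of data collection at participating schools across three time-points".
- **Movement competence:** those tests are held "within the school hall or playground and video-recorded for later analysis". Nothing similar is stated for the RCS.

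**The concern.** The RCS records an observer's impression of a child on scales such as vulnerable versus invincible. It is not a count or a timing, so a rater's expectation can enter the score directly. The hypotheses rank all three arms on self-regulation, so a rater who knows the arm knows the expected ordering.

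The practical reasons clearly apply to teachers and coaches, who deliver or witness the lessons, and to research staff who train the coaches, meet them weekly or observe lessons. They do not obviously apply to someone whose only task at a school is to rate an obstacle course. The blinding statement treats both groups alike.

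At stake is the self-regulation conclusion. A lean in the ratings shifts the estimated difference by its full amount at any sample size, and the planned mixed models cannot separate it from a true effect. The SDQ offers no protected second reading of the construct.

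**Working it through.** **1. Is any self-regulation measure masked?**

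| Measure | Rater | Rater's status under Blinding and Randomization |
|---|---|---|
| SDQ | Class teacher | Unblinded |
| RCS | Researcher (trained observer) | Unblinded |

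The article provides no masked rater, no scoring from film and no independent second rating for the RCS. The answer is no.

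**2. Is there an expectation for a rater to act on?** Yes. The Hypotheses section puts both interventions above control, and Non-linear above Linear, on self-regulation.

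**3. Could some raters be kept unaware of the arm?** The article neither states nor excludes this. Trained assistants are planned at all three time points. However, the Process Evaluation section says "Direct observations of PE lessons by researchers and coaches’ logs will be used", and it also has trained researchers seeing children individually after observed lessons, and research assistants timing and filming there. Staff numbers are not given, so the number of people free of those roles is unknown.

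**4. Scale structure.** Subscale ranges are items × 1 to items × 7: Cognitive 6 to 42, Affective 7 to 49, Physical/Motor 3 to 21, and 6 + 7 + 3 = 16 items. These agree with the article.

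**5. Illustration of size (lean and SD are both assumptions).** The article gives neither an RCS standard deviation nor a rater effect. Assume the same lean on every item, in one direction, differing between arms.

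- Lean of 0.25 per item: 6 × 0.25 = 1.5 points on the Cognitive subscale.
- Lean of 0.5 per item: 6 × 0.5 = 3.0 points.
- Assumed SD of 8: 1.5/8 = 0.19 and 3.0/8 = 0.38 SD.
- Assumed SD of 6: 1.5/6 = 0.25 and 3.0/6 = 0.50 SD.

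**6. Effect on a test when there is no true difference.** Inputs from Sample Size and Statistical Power: design effect 1 + (20 − 1) × 0.16 = 4.04, and 54 × 4.04 = 218 children. Both reproduce the stated figures. The ICC of 0.16 is for movement competence and is borrowed here. Take two arms of 218/3 = 72.7 children:

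SE = √[4.04 × (1/72.7 + 1/72.7)] = 0.333 SD

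For a lean of b SD, the chance of a significant result at two-sided 0.05 is Φ(b/SE − 1.96) + Φ(−b/SE − 1.96).

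| Assumed lean b (SD) | Chance of a false positive |
|---|---|
| 0 | 5% |
| 0.1 | 6% |
| 0.2 | 9% |
| 0.3 | 15% |
| 0.4 | 22% |

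A split of 54.5 against 109 children gives the same figures.

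**The case against.** The strongest reply is that the lack of blinding is disclosed with a reason, that the sections agree with one another, and that the RCS is one of several secondary outcomes. All of that is correct. There is no contradiction or concealment, and the primary outcome is not in question here. But disclosure does not protect the measure, and the stated reason does not distinguish raters from people who must know the arm.

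A reader might infer more than the documents support, in four ways:

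- **That existing assistants could certainly rate without knowing the arm.** This is only an inference. Researchers and assistants attend lessons, and staffing is not described.
- **That the bias is as large as the planned effect.** Lean and SD are both assumed. A shift of 0.4 SD needs the largest lean together with an SD of 7.5 or less (3.0/7.5 = 0.4). The article's d = 0.4 also concerns movement competence, not the RCS. Small leans of 0.1 to 0.2 SD raise the false-positive rate only to about 6 to 9%.
- **That the ratings will be biased.** The plan leaves that possible; it does not make it certain.
- **That the mediation analyses rest on these ratings.** The mediators in Data Analysis are actual and perceived movement competence. Self-regulation could enter only as a downstream outcome.

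It can also be said that the blanket statement covers the video-coded movement tests, where masked coding would be easier. That is fair, and narrowing the statement would help there too. It does not remove the gap for the RCS.

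**Conclusion.** The point holds as a weakness of design in a secondary outcome. A subjective rating with directional hypotheses is scored by people declared unblinded, and the only other measure of the construct is completed by unblinded teachers. This conclusion follows from the text and needs no numerical assumption.

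The size of any bias is unknown. The 0.19 to 0.50 SD range depends entirely on the assumed lean and SD, and shows only that modest leaning could matter. The false-positive figures rest further on a borrowed ICC and assumed arm sizes. Whether masked rating is achievable at every school cannot be settled from the article, so the change should be made as far as staffing permits.

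**What to change.** 1. Limit the blinding statement to teachers, coaches and the staff who train, support or observe them, and describe outcome raters separately.
2. As far as existing staffing allows, assign RCS rating at T1 and T2 to the trained assistants already planned, choosing people who have not trained coaches or observed lessons at that school and who are not told its arm.
3. Do the same at T0 if allocation is already known by then. The article places randomization after headteacher consent but does not say whether it precedes baseline. Unmasked baseline ratings followed by masked later ones could add an error of their own.
4. Record for each visit whether masking held. Where it did not, report the RCS results as unblinded ratings. If the visits dated in the Design section (last planned for January–February 2019) are complete, what remains is to report who rated the RCS and what they knew.

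**Cost.** Rostering becomes less flexible, fewer people can serve as raters, and some unmasking on site is likely.

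**Optional alternative.** Film the obstacle course and have it rated masked to arm. This has a real coding cost: at 10 to 15 minutes per child, 314 children and three waves, 314 × 3 × 10/60 = 157 hours to 314 × 3 × 15/60 = 236 hours of footage. The article does not say whether RCS scores from film are equivalent to live scores.

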##### Anthropometrics

Children’s height, sitting height, waist and body mass will be measured with an accuracy of 0.1 cm and 0.1 kg, respectively (Lohman et al., 1988). Height and sitting height will be assessed with a portable stadiometer (Leicester Height Measure, SECA, Birmingham, United Kingdom) and body mass will be assessed using digital scales (Tanita WB100-MA, Tanita Europe, Netherlands). Waist circumference will be measured around the navel region. Measurements will be taken without shoes and whilst wearing light clothing, taking approximately 5 min. Height and weight values will be used to examine weight status through the International Obesity Task Forces age and sex adjusted body mass index (BMI) growth-reference to enable international comparisons (Cole et al., 2000).

### Process Evaluation

Informed by the RE-AIM framework and previous literature (Glasgow et al., 1999; Linnan et al., 2002) as well as by the UK Medical Research Council guidance for process evaluation that advocates exploring context, implementation, impact and outcomes (Moore et al., 2015) a pragmatic process evaluation design will examine intervention *context*, *reach*, *dose*, *fidelity*, *acceptability implementation*, *impact*, *acceptability*, and *sustainability*.

*Reach* will be assessed using school administrative data on child demographics and school registers. Teachers (control schools) and SAMPLE-PE coaches (intervention schools) will be asked to log the number of PE lessons implemented at each school, and the duration of each PE lesson in minutes to determine. Direct observations of PE lessons by researchers and coaches’ logs will be used to examine *dose delivered*, *fidelity* and participant responsiveness (*dose received*). Specifically, in each intervention and a subsample of control schools, three lessons from each class (one in every 5-week phase of delivery) for a total of approximately 50 lessons will be audio- and video- recorded, using a wireless microphone and video camera (situated to capture the whole class and deliverer).

Video footage will subsequently be analyzed by trained researchers to assess whether the intervention was delivered as intended (*fidelity*) using developed observation checklists for Non-linear and Linear pedagogies, respectively. Intervention fidelity will be confirmed if (i) the Non-linear pedagogy intervention schools’ PE lessons show greater implementation of Non-linear pedagogical principles than Linear and control schools PE lessons, and (ii) the reverse is true for Linear pedagogy intervention schools’ PE lessons. Video recordings of PE lessons will also be retrospectively coded using established observation checklists to examine SAMPLE-PE coach (intervention schools) and teacher (control schools) behaviors in relation to promoting children’s moderate-to-vigorous physical activity (SOFIT+; Weaver et al., 2016; Fairclough et al., 2018) and supporting or thwarting children’s psychological needs for relatedness, competence, and autonomy (Smith et al., 2015). Researchers will also record the number of children participating in lessons, and the number of staff present and collect data on the themes and types of activities undertaken within the control group’s PE lessons.

*Participant responsiveness*. refers to how responsive participants are to an intervention (Durlak and Dupre, 2008). For the purposes of this process evaluation, we will examine participant responsiveness in terms of children’s self-determined motivation, psychological needs satisfaction and physical activity levels within the observed PE lessons (15 lessons at each three time points). Psychological need satisfaction and enjoyment of the PE lesson from a child perspective will be assessed at the end of each observed PE lesson. Physical activity will be assessed during each observed lesson. In terms of self-determined motivation, immediately following the lesson, all research children (those within both experimental arms and three control schools) will complete brief measures of relatedness, autonomy and competence need satisfaction on a 1:1 basis with trained researchers. For relatedness, we will look to explore the quantity of social interactions. In line with Sebanc (2003) children will be asked by a member of the research team to identify which children within their class they worked with during that lesson from a school class photo list. For competence, children will be asked *how good were you at things during that PE lesson?* This will be measured on a 1–5 star rating scale: 1 being not very good and 5 being very good. For autonomy, children will be asked *did you get to do any choosing during that PE lesson?* The answer format is on a two-layer response where they first choose either ‘yes’ or ‘no.’ Depending on their initial response, they will be asked if this is ‘sometimes yes’ or always yes,’ or ‘sometimes no,’ or ‘always no.’ For enjoyment, as children leave the PE lesson, they will be asked to tap on 1 of 3 posters situated on a wall by the exit door displaying an emoji face depicted either as boring, ok or fun. Children’s actions will be video recorded by a research assistant. To assess participant responsiveness in terms of physical activity levels, a sub-sample of children (50% of the research participants in each class) will be randomly-selected to wear an Actigraph GT9X+ accelerometer (Actigraph, Pensacola, FL, United States) on their non-dominant wrist within each PE lesson observation. The time that the teacher commences and ends the lesson will be recorded by a research assistant, and used to calculate the proportion of time children spent in moderate-to-vigorous physical activity.

A qualitative methodology, will be utilized to explore the experiences and perceptions of key stakeholders within intervention schools with regards to *context*, *fidelity*, *implementation*, *impact*, and *acceptability*, and *sustainability*. Utilizing the interpretivist paradigm, it is recognized that human action and interaction such as PE lessons, is experienced subjectively evaluated through individual meaning making (McKenzie et al., 1997). Thus, the effectiveness of an intervention, such as SAMPLE-PE, is inherently linked to the experiences and perceptions of key stakeholders such as teachers. Collecting and analyzing these perceptions, through interpretivist qualitative methods is, therefore, an essential part of a process evaluation (Cheng and Metcalfe, 2018). To that end, qualitative methods are an appropriate methodology to gather data (Smith and McGannon, 2018).

Through interviews, researchers will explore: (1) the *fidelity* of the intervention; (2) *implementation* and *impact*; and (3) *acceptability* and *sustainability* of *Linear* and Non-linear pedagogy intervention curriculums. The sample is purposive in that individuals with the experience of intervention will be recruited. It is also iterative, because as the intervention proceeds, the sample size may increase to include other stakeholders, e.g., teaching assistants. Importantly, the process evaluation not only gathers the experiences and perceptions of stakeholders such as teachers, but a process evaluation can also describe the context in which interventions were experienced. This will be captured through structured interviews with head teachers of intervention schools who are well-placed to describe the school as a whole. These interviews will explore school policy, funding, support, equipment, time allocation for PE, and potential for scale-up of the interventions, as well as any other aspects of the complex school environment that may have influenced the intervention and outcomes.

To collect interview data, a combination of skype, face-to-face and email interviews will be utilized. More specifically, participants will be offered the opportunity to share their experiences and perceptions in the format that best enables them to do so. This choice enables participants to exercise their autonomy (Orb et al., 2001). Structured interview schedules have been developed (Supplementary File 3) in order to focus attention on the context, fidelity, implementation, impact, acceptability and sustainability of the intervention across both *Linear* and Non-linear Pedagogy schools. The use of a structured interview schedule will ensure that interviews will be conducted in a consistent manner regardless of medium, e.g., face-to-face or email. The structured format of the interview schedule will also ensure that any researcher bias is ‘managed’ in order to maintain equipoise as far as possible (Eborall et al., 2014). Interviews will be transcribed and analyzed using thematic analysis (Clarke and Braun, 2013). To ensure rigor during the data collection and analysis processes, co-researchers will act as critical friends (Smith and McGannon, 2018). This will involve reviewing the structured interview schedule to identify leading questions, and reviewing coding and themes to ensure verisimilitude with the data.

